## Abstract

**Introduction:**

In patients treated for cardiac disease, loneliness is known to contribute negatively to health behavior, health outcome, and increase risk of cardiac and all-cause mortality. Even so, in health care research, social support interventional studies targeting patients who experience loneliness are lacking.

**Aim:**

To determine the feasibility of an individually structured social support intervention targeting patients treated for cardiac disease who experience loneliness.

**Design:**

A feasibility study based on randomized clinical trial design with 1:1 randomization to a 6-month social support program, plus usual care (intervention) versus usual care, (i.e., regular guidelines-based follow-up). Intervention: Patients classified as high risk lonely according to the High Risk Loneliness tool will be provided with an informal caregiver in the 6 months rehabilitation phase following cardiac disease treatment. The informal caregiver will be designated by the patient from the existing social network or a peer, depending on patients’ preferences. The core content of the intervention is through nurse consultations at baseline and 1, 3, and 6 months, to enhance and reinforce the informal caregiver’s competences to be a social support resource. The theoretical framework of the nurse consultations will be based on middle-range theory of self-care.

**Outcome:**

Feasibility will be evaluated in terms of acceptability and adherence according to predefined feasibility criteria. The preliminary effect of the intervention on patient-reported outcomes, health behaviors, and health outcomes will be evaluated in the intervention and the control group at baseline and 1, 3, 6, and 12 months.

**Discussion:**

The present study will contribute with knowledge on how to implement a feasible social support intervention targeting patients treated for cardiac disease who experience loneliness and, furthermore, investigate the preliminary effect on health behavior and health outcome in the early rehabilitation period.

**Trial registration:**

The trial is registered on clinicaltrials.gov (NCT05503810) 18.08.2022.

## Introduction

Cardiac disease is a major cause of impaired quality of life and the leading cause of mortality worldwide [1]. In Denmark, approximately 27,000 people are treated for cardiac disease, i.e., ischemic heart disease with coronary artery bypass grafting (CABG) or percutaneous coronary intervention (PCI), valve disease with transcatheter aortic valve replacement (TAVR) or surgical aortic valve replacement (SAVR), and arrhythmia with implantable cardioverter defibrillator (ICD), pacemaker implantation, or ablation [2]. One of the psychosocial factors that is known to contribute negatively to cardiac patients’ health behavior [3, 4], health outcome [5, 6], and cardiac and all-cause mortality [7–10] is loneliness. To illustrate, in a national study including 14,000 patients across cardiac diagnosis, it was found that feeling alone doubled 1-year mortality in analyses adjusted for baseline health status [9].

Loneliness can be defined as follows: “A distressing feeling that accompanies the perception that one’s social needs are not being met by the quantity or especially the quality of one’s social relationships” [11].

The link between loneliness and health outcomes is explained by two main hypotheses: (1) social support increases the feeling of trust and safety which helps to “buffer” the potentially harmful influences of stress-induced cardiovascular reactivity and (2) social support increases the motivation to make healthier choices [12, 13]. Besides, the impact of loneliness on health behaviors and health outcomes, and of similar importance, is that patients experience social support from network members as vital in order to handle the physical and psychological aftermath from in-hospital cardiac disease treatment [14–16]. This increased need for social support places patients with inadequate or sparse social support in a vulnerable situation in the early rehabilitation period.

Overall, the evidence on the link between loneliness and health has led to an elevated interest in intervening in this matter. Also, the European guidelines on cardiovascular disease prevention recommend the inclusion of a lack of social support as one of the core psychosocial risk factors in clinical practice [17]. However, in health care research, social support interventional studies targeting patients who experience loneliness is lacking. Therefore, it has yet to be demonstrated how to provide a feasible social support intervention and if improvement in perceived social support leads to improvements in health outcomes [18].

In the social integration literature [19–22], it is argued that interventions should be underpinned by a theoretical framework to increase the likelihood of achieving success. In this matter, social support interventions involving informal caregivers from patients existing social network have shown positive results. Also, caregiver-oriented strategies and psychological counseling have shown promising results on decreasing loneliness [23].

When structuring a social support intervention, evidence points that the intervention should be fitted to the needs and characteristics of the target population and, therefore, that it is advantageous to involve the target population in the design of the intervention [21]. In our own previous research, we have used patient involvement to illuminate potential preferences and barriers toward a social support intervention in patients with cardiac disease who experiences loneliness [24]. In this study, it was revealed that the intervention must meet the patient's individual preferences in relation to, e.g., the type of informal caregiver that provides the social support needed and intervention start-up time, frequency, and duration, in order to be an attractive proposition.

Based on findings from the patient involvement sessions, alongside the existing literature on loneliness and social support interventions, a study protocol for an intervention study targeting patients treated for cardiac disease who experience loneliness has been developed. As no previous studies have investigated an individually tailored social support intervention in this patient population, this initial study will be conducted as a feasibility trial [25]. Feasibility as a research method is chosen because it will provide valuable knowledge on acceptability, adherence, and attrition, as well as monitor potential deficiencies in the structure of the intervention.

## Study hypothesis

We hypothesize that an individually structured social support intervention targeting patients with cardiac disease who experience loneliness has the potential to decrease loneliness which in turn decreases stress-induced cardiovascular reactivity and promotes health behaviors which altogether will be reflected in patients’ wellbeing and in health outcomes.

## Study aims and objectives

The primary aim of the study is to determine the feasibility of an individually structured social support intervention targeting patients treated for cardiac disease who experience loneliness.

The secondary aim is to explore the preliminary evidence on the effect of the intervention on health behaviors and health outcomes. The results will be used to perform a sample size calculation in a potential future larger trial [26].

## Design and method

The protocol is based on reporting guidelines from the SPIRIT guideline for Standard Protocol Items for Clinical Trials [27] adapted as recommended when reporting protocols of feasibility trials [28].

## Trial design

A feasibility study based on randomized clinical trial (RCT) design. The RCT design with 1:1 randomization to a 6-month social support program, plus usual care (intervention) versus usual care, (i.e., regular guidelines-based follow-up [29], will provide preliminary evidence on the effect of the intervention on patient-reported outcomes, health behaviors, and health outcomes. To investigate the sustainability of a potential long-term effect of the intervention, the follow-up period will be 1 year.

### Sample size

As the primary aim of this study is to test feasibility, there is no requirement for a formal power calculation [30]. Considerations about the sample size are related to the fact that no previous studies have investigated a social support intervention targeting patients with cardiac disease who experience loneliness and, therefore, no data exists on acceptability to the intervention. A sample size of 40 was chosen as it seems reasonable to exploratory investigate the feasibility, in particular acceptability, in a small sample and at the same time have a sample size big enough to investigate the additional aspects that are being assessed for feasibility [31]. Consequently, the study will include 20 patients and 20 informal caregivers in the intervention group and 20 patients in the control group. A flowchart of the trial is presented in Fig. 1.

**Fig. 1 Fig1:**
[figure not shown]
Flowchart

## Trial population, eligibility criteria, and randomization

### Patients

Inclusion criteria: Three treatment groups, IHD (CABG or PCI), valve disease (TAVR, SAVR, surgical mitral valve procedures), and arrhythmia (ICD, pacemaker implantation or ablation) treated at Rigshospitalet and classified as high risk lonely according to the High Risk Loneliness (HiRL) tool [10], are given oral and written information about the study design and asked for permission to be contacted within 1 week from discharge to home. The HiRL screening tool has not yet been validated, but previous research suggest that the tool has a prognostic value for 1-year mortality, i.e., sensitivity 19.9% and specificity 89.5%, in patients treated for IHD. The HiRL screening tool is presented in Table 1. The final decision on participation must be taken by the patient within one week of discharge and patients will sign informed consent.

**Table 1 Tab1:** High Risk Loneliness (HiRL) screening tool

Screening question	Answer	Point	Classification of high-risk loneliness
“Does it ever happen that you are alone even though you wish to be with others?”	No		≥ 1 point
	Yes, but rarely		
	Yes, sometimes		
	Yes, often	1	
“Do you have someone to talk to if you experience problems or need support?”	Yes, often		
	Yes, most of the time		
	Yes, sometimes		
	No, never or almost never	1	

Exclusion criteria: Patients who are unable to provide written consent; thus, patients with severe cognitive or physical dysfunction will not be approached.

Randomization: Patients will be identified and screened consecutively. Randomization is completed using the web-based tool Randomizer for Clinical Trials. Patients will be stratified according to gender.

Patients who accept participation and who are included in the intervention group will receive further oral and written information about the intervention structure and sign informed content. In relation to this, they will be asked about their preference for the choice of an informal caregiver and for the structure of the intervention.

### Informal caregivers

The informal caregiver is identified by the patient from two of the following options:

Social network member: This type of informal caregiver will be designated by the patient from the existing social network (e.g., a partner, friend, or neighbor), and the patient will be asked to initiate the contact with the social network member. If he/she accepts to be an informal caregiver, the intervention staff will contact the informal caregiver and give oral and written information, and if acceptance is confirmed, an inclusion-consultation will be performed subsequently. The consultation can be performed in-person or remote (phone or virtually). This consultation aims at investigating the potential caregiver’s prerequisites, resources, and motivation to participate with minimal risk of suffering from caregiver burden.

Exclusion criteria: Potential informal caregivers who are assessed as not having the necessary prerequisites or do not speak or understand Danish.

If the social network member does not accept to be an informal caregiver or if he/she is deemed to be at risk of caregiver burden, the patient will be given the opportunity to point out an alternative social network member to be an informal caregiver or to choose a peer as an informal caregiver.

Peer: This type of informal caregiver is defined as a person with similar disease as the recipient. The peer will be recruited by the Danish Heart Foundation from among volunteers in the existing peer support program.

## Overall intervention structure

The core content of the intervention is through nurse consultations to enhance and reinforce the informal caregiver’s competences to be a social support resource. The intervention structure is based on the evidence on the positive impact of support provided by a peer (a person with similar disease as the recipient) [18, 32] or by a network member [23, 33] and the findings from patient involvement interview sessions performed by the project group [24]. Therefore, the patient will be provided with an informal caregiver in the long-term (6 months) rehabilitation phase following cardiac disease treatment. The role of the informal caregiver as a social support resource will be the same independent of which type of caregiver (social network member or peer) the patient has chosen. After choosing the type of informal caregiver, the patient will be asked about preferred frequency and form of contact with the informal caregiver. The patient and the informal caregiver are encouraged to be in contact a minimum of once a week in-person or remote (phone or virtually). The intervention staff will contact the informal caregiver and ask for acceptance of the suggested structure. If a need for adjustment of frequency or form occurs in the intervention period, patients and informal caregivers may arrange this together or in consultation with the intervention staff.

Furthermore, the patients will receive motivational text messages intended to enhance the supportive environment [34]. The text messages will be formulated by the research group and will be sent automatically to the patient on Mondays between 1 and 3 pm by a text message gateway “cpsms.” The wording of the text messages can, for example, be “*The choices you make today shape the life you live tomorrow*” or “*Success is the sum of small efforts repeated*.”

At enrollment, 1 month, and 3 and 6 months, an intervention nurse will contact the informal caregiver and provide guidance and counseling based on a theoretical framework derived from complementary fields, i.e., psychology with the theory of dyadic processes [12, 35] and nursing with self-care theory [36, 37]. These theoretical frames will inform the intervention nurse on which domains to focus on when guiding the informal caregiver. An intervention guide for the nurse is used in all nurse consultations. A description of the aim and method for each consultation described in the intervention guide is shown in Table 2.

**Table 2 Tab2:** Aim and method for each nurse consultation with the informal caregiver

Enrollment	One month	Three months	Six months
• For the nurse, to gain insight into the informal caregiver's prerequisites • To provide information to the informal caregiver about the role as “HeartBuddy” • Guidance and counseling in emotional support, i.e., encourage the informal caregiver to ask the patient open and curious questions about their well-being and everyday life, and, to listen without prejudice or neglecting patient thoughts and feelings • Guidance and counseling in informational support related to patients’ health behavior and self-care, i.e., maintenance, monitoring, and management	• Gain insight into the relational processes between patient and informal caregiver and provide guidance in relation to potential challenges • Guidance and counseling in emotional support • Guidance and counseling in informational support related to patients’ health behavior and self-care	• Gain insight into the relational processes between patient and informal caregiver and provide guidance in relation to potential challenges • Guidance and counseling in emotional support • Guidance and counseling in informational support related to patients’ health behavior and self-care	• Guidance in relation to ending the role as “HeartBuddy”

The central themes are furthermore described in an easy-to-read langue, to be handed out to the informal caregiver as a pamphlet “Guide to HeartBuddy.”

Both patient and informal caregiver will be provided with the possibility of contacting an intervention nurse through an open hotline (workdays, daytime) if any additional questions arise during the intervention period.

## Outcomes

### Feasibility

The outcomes of the feasibility study will inform the design of a potential upcoming randomized control trial (RCT). The feasibility will be evaluated in terms of acceptability and adherence [38, 39]. Feasibility criteria are based on the balance between the financial and logistical resources of the intervention and the expected effect.

The feasibility criterion for acceptability in patients is supported if 25% of patients who are screened as lonely agree to participate in the trial.

The feasibility criteria for acceptability in social network members is supported if 50% of invited social network members accept participation and are assessed to have the prerequisites to be an informal caregiver.

The feasibility criteria for adherence in patients is supported if 75% adhere to the intervention, i.e., have contact with the informal caregiver once a week for a minimum of 8 out of 12 weeks.

The feasibility criteria for adherence in informal caregivers (social network member or peer) is supported if 75% participate in three out of four consultations. An overview of the feasibility criteria is presented in Table 3.

**Table 3 Tab3:** Feasibility measurement, measurement definition, and feasibility criteria

Feasibility measurement	Measurement definition	Feasibility criteria
Acceptability	• Percentage of eligible patients who agree to participate in the trial • Patients’ choice of type of informal caregiver *Measures of social network members as informal caregivers*: • Percentage of potential caregivers who accepts to be an informal caregiver • Percentage assessed to have prerequisites to be an informal caregiver	25% of patients who are screened and found to be lonely agree to participate in the trial 50% of invited social network members accept participation and is assessed to have prerequisites to be an informal caregiver
Adherence	• Percentage of informal caregivers participating in all three intervention consultations with the trial staff • Percentage in contact with the patient at least once a week face to face, by phone or virtually	75% of informal caregivers participate in three out of four consultations 75% of included patients adhere to the intervention, i.e., having contact with the informal caregiver once a week for a minimum of 8 out of 12 weeks
Loss to follow-up	• Percentage of patients and informal caregivers who do not complete the trial	A maximum of 25% of informal caregivers do not attend two out of three intervention consultations with the trial staff attend A maximum of 25% of patients do not complete the trial
Resource consumption	• Time resources used to include study participants • Time resources used to complete the three nurse consultations	N/A for feasibility

In feasibility and pilot testing, it is furthermore recommended that the resources used to complete the study is monitored [30]. This will be done by keeping a record of time resources used to include study participants and to complete the four nurse consultations (enrollment, 1 month, 3 and 6 months) and also frequency and time used on the additional questions from patients and informal caregivers to the open hotline.

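### Table 3 measures caregiver adherence on three consultations but tests it on four, so the adherence measurement and its 75% criterion do not match

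*Protocol article*

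**What the plan says.** Outside Table 3 the article consistently gives four consultations. The section on overall intervention structure says "At enrollment, 1 month, and 3 and 6 months, an intervention nurse will contact the informal caregiver", Table 2 has four columns, and the paragraph after Table 3 undertakes to record the time needed "to complete the four nurse consultations (enrollment, 1 month, 3 and 6 months".

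Table 3 in the Feasibility section is not consistent with this:

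- Adherence, measurement column: "Percentage of informal caregivers participating in all three intervention consultations with the trial staff".
- Adherence, criteria column: "75% of informal caregivers participate in three out of four consultations". The running text above the table sets the same threshold.
- Loss to follow-up, criteria column: "A maximum of 25% of informal caregivers do not attend two out of three intervention consultations with the trial staff attend". The sentence is garbled. The measurement beside it is the percentage of patients and caregivers not completing the trial, which is not an attendance count.
- Resource consumption: "Time resources used to complete the three nurse consultations".

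Three entries in the table therefore rest on three consultations. The adherence criterion and everything outside the table rest on four.

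**The concern.** The primary aim is to determine feasibility, judged by predefined acceptability and adherence criteria, and the nurse consultations with the caregiver are described as the core of the intervention. In the adherence row, the quantity to be measured is not the quantity to be tested. A caregiver who misses one later consultation satisfies the criterion, but may not count under the measurement. An analyst who tabulates the measurement as defined and compares it with 75% can reach the opposite conclusion from one who follows the criterion. If the choice is still open when attendance is known, it could decide whether caregiver adherence is declared supported.

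The loss row adds a second difficulty: its criterion does not test its own measurement, and its denominator of three is unexplained.

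**Working it through.** The article gives no figure to reproduce here, since it makes no power calculation. The check is whether the same attendance data can give different answers.

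**Inputs from the article.** Four consultations; 20 informal caregivers (Sample size section); a 75% threshold, so 0.75 × 20 = 15 caregivers are needed.

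**Assumptions not in the article.** Enrollment is attended by every caregiver. Each later consultation is attended independently with probability q, shown over a range. The count of three means months 1, 3 and 6 unless stated otherwise.

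**Step 1: a worked case.** Of 20 caregivers, 12 attend all four consultations, 4 attend enrollment plus two, and 4 attend enrollment plus one.

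- All three: 12/20 = 60%, below 75%.
- Three of four: (12 + 4)/20 = 80%, above 75%.
- Two of three (loss row): (12 + 4)/20 = 80% meet it, so 20% do not, within the 25% limit.

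**Step 2: chance of reaching 15 of 20.** The probability that one caregiver qualifies is q³ for all three. For three of four with enrollment attended it is q³ + 3q²(1 − q). At q = 0.80 these are 0.512 and 0.512 + 3 × 0.64 × 0.20 = 0.896. The chance of at least 15 of 20 is the binomial upper tail.

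| q | All three, per caregiver | Three of four, per caregiver | P(≥15/20), all three | P(≥15/20), three of four |
|---|---|---|---|---|
| 0.70 | 0.343 | 0.784 | <0.001 | 0.749 |
| 0.80 | 0.512 | 0.896 | 0.027 | 0.986 |
| 0.85 | 0.614 | 0.939 | 0.154 | 0.999 |
| 0.90 | 0.729 | 0.972 | 0.532 | >0.999 |
| 0.95 | 0.857 | 0.993 | 0.945 | >0.999 |

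**Step 3: if enrollment can also be missed at the same rate.** Three of four becomes q⁴ + 4q³(1 − q). At q = 0.80 this is 0.819, and the chance of 15 of 20 is 0.862, still far from 0.027. At q = 0.70 that chance is 0.250.

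**Step 4: the other reading of three (enrollment, 1 and 3 months).** All three is then q². At q = 0.80 this is 0.64 with a 0.217 chance of 15 of 20; at 0.90 the chance is 0.836 and at 0.95 it is 0.99. The gap is smaller but remains. The loss row also separates from adherence. Suppose 12 attend all four, 2 attend enrollment, 1 and 3 months, 4 attend enrollment and 1 month only, and 2 attend enrollment only. Three of four is 14/20 = 70% and fails. Two of three is 18/20 = 90%, so only 10% count as lost and that criterion passes.

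**The case against.** The best defense is that the adherence threshold itself is stable. The 75% is attached only to three out of four, with the same meaning in the running text and in Table 3. The all-three wording sits in the measurement column and carries no threshold, and two out of three belongs to a separate row on loss. A careful analyst would probably follow the criterion and get one answer. This stands. A reader might infer that one criterion is judged by three incompatible rules, and the article does not support that. What remains is that the paired measurement does not yield what the criterion tests.

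A reader might also infer that adherence and caregiver loss are one test counted twice. That holds only if enrollment is always attended and three means months 1, 3 and 6. The article does not settle the second condition, and under the reading in Step 4 the two rows can disagree. On the first condition, the article says that "an inclusion-consultation will be performed subsequently" for a social network member who accepts. It describes no such step for peers, and it does not say that this contact is the same as the enrollment consultation. Universal attendance at enrollment is therefore an assumption.

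Finally, the attendance rates and independence are not from the article, and at high attendance the two definitions nearly agree. That limits the size of the effect but does not remove the contradiction. Nor does the feasibility setting, because these criteria are how the primary aim is judged.

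**Conclusion.** Table 3 is wrong as written. It conflicts with the four-consultation schedule and, in the adherence row, with itself. The consequence is conditional: the conclusion can reverse if the 75% is applied to the measurement as defined, as in the case giving 60% against 80%. With enrollment attended by all and three read as months 1, 3 and 6, the chance of reaching the threshold differs most at moderate attendance (0.03 against 0.99 at 80%) and little at 95% (0.95 against more than 0.999). These probabilities rest on assumed, independent attendance. The contradiction in wording rests on no assumption.

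The problem affects one of the four feasibility criteria in the running text, together with the caregiver loss and resource rows of the table.

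**What to change.** Settle the following before attendance results are seen:

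1. Make the adherence measurement match the stated criterion: the percentage of all enrolled caregivers who attend at least three of the four scheduled consultations (enrollment, 1, 3 and 6 months). Also report attendance at the three post-enrollment consultations, which shows how far the enrollment contact carries the result.
2. Correct the resource row to four consultations.
3. Restate the caregiver loss criterion so that it tests non-completion, as its measurement says, with a named denominator and the 25% limit kept. If loss is to stay attendance-based, name the consultations counted and note the conditions under which it repeats the adherence criterion.

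Items 1 and 2 cost only rewording, since the existing criterion already needs attendance recorded at each consultation. Item 3 is also rewording, provided that what counts as a caregiver completing the trial is already recorded; the article does not say.

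### Table 3 sets the caregiver loss-to-follow-up limit on consultation attendance, not on the row's own measure of completion, so it gives no independent verdict on caregiver retention once caregiver adherence is met

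*Protocol article*

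**What the plan says.** All of this is in the protocol article.

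- **Loss to follow-up, measurement (Table 3):** "Percentage of patients and informal caregivers who do not complete the trial". One measure covers both groups.
- **Loss to follow-up, patient limit (Table 3):** "A maximum of 25% of patients do not complete the trial". This applies the measure.
- **Loss to follow-up, caregiver limit (Table 3):** "A maximum of 25% of informal caregivers do not attend two out of three intervention consultations with the trial staff". This applies attendance. The sentence ends with a stray second verb.
- **Adherence, caregiver criterion (Table 3 and the Feasibility text):** "75% of informal caregivers participate in three out of four consultations". The measurement column beside it instead reads "Percentage of informal caregivers participating in all three intervention consultations with the trial staff".
- **Schedule (text after Table 3):** time is recorded "to complete the four nurse consultations (enrollment, 1 month, 3 and 6 months"), so there are four consultations. Table 3 speaks of three in several places and never says which three.
- **Program length (Overall intervention structure):** "the patient will be provided with an informal caregiver in the long-term (6 months) rehabilitation phase".
- **Number of caregivers (Sample size):** "the study will include 20 patients and 20 informal caregivers in the intervention group".

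**The concern.** The row announces one quantity and then sets the caregiver threshold on another. The caregiver rule depends only on a count of visits attended. Whether the caregiver was still in the role at 6 months does not enter it. The last scheduled visit before the end is at 3 months, so withdrawals in the second half of the program can escape the rule.

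The attendance threshold also sits beneath a stricter attendance threshold in the Adherence row. It therefore looks like a second check but may not be one.

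The Introduction gives attrition as one of the things the feasibility design was chosen to learn, and the Feasibility section says the outcomes will inform a possible later randomized trial. How many caregivers last 6 months is a central planning figure for that trial, and this row holds the only pass mark that is labelled as addressing it.

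**Working it through.** The plan derives no figure for this criterion, so there is nothing to reproduce. The check is logical first, then numerical.

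**Inputs.** Visits at enrollment (E), 1, 3 and 6 months; 20 caregivers; adherent = at least 3 of 4 visits; lost = fewer than 2 of a set of three visits; limit 25% of 20 = 5. Because the three visits are not named, all four possible sets were tried. Reading the garbled sentence as missing at least two of three gives the same caregivers scored as lost.

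**Step 1: caregivers who attend every visit and then stop.**

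| Last visit attended | Adherent (3 of 4)? | Lost, set E/1/3 or E/1/6 | Lost, set E/3/6 or 1/3/6 | Completes? |
|---|---|---|---|---|
| E | no | yes | yes | no |
| 1 month | no | no | yes | no |
| 3 months | yes | no | no | no |
| 6 months | yes | no | no | yes |

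The 3-month row is the defect: under every set, that caregiver is adherent and not lost, yet does not complete. The 1-month row depends on which three visits are meant.

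**Step 2: nesting.** A caregiver who attends at least 3 of 4 misses at most one visit, so misses at most one of any three and attends at least two of them. Enumerating all 2^4 = 16 attendance patterns under each of the four sets finds none that is both adherent and lost. With a common denominator of 20, adherence passes at 15 or more (15/20 = 75%), leaving at most 20 − 15 = 5 who could be lost (5/20 = 25%), which meets the limit. The same holds if adherence means attending all three of the same three visits.

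With different denominators the implication can break. Adherence of 14/18 = 77.8% passes, while 6/20 = 30% lost would fail.

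**Step 3: boundary case.** If all 20 leave after the 3-month visit, adherence is 20/20 = 100%, loss as written is 0/20 = 0%, and non-completion is 20/20 = 100%.

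**Step 4: illustration.** Assume a constant withdrawal hazard h, attendance at every visit until withdrawal, and independent caregivers. For 6-month non-completion q:

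- h = −ln(1 − q)/6 per month
- P(scored lost), set E/1/3 or E/1/6 = 1 − exp(−h), i.e. leaves before month 1
- P(scored lost), set E/3/6 or 1/3/6 = 1 − exp(−3h), i.e. leaves before month 3
- P(pass) = P(X ≤ 5), X ~ Binomial(20, P(scored lost)); for a completion-based limit use q itself

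| q | h | P(lost), E/1/3 | P(lost), 1/3/6 | P(pass), E/1/3 | P(pass), 1/3/6 | P(pass), completion |
|---|---|---|---|---|---|---|
| 0.40 | 0.0851 | 0.082 | 0.225 | 0.996 | 0.714 | 0.126 |
| 0.50 | 0.1155 | 0.109 | 0.293 | 0.983 | 0.444 | 0.021 |

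**The case against.** Several points on the other side are fair.

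*Completion is already listed.* A reader might infer that caregiver attrition will go unreported. The documents do not support that: the row's measurement column covers caregivers who do not complete, so the boundary case would show as 100% non-completion. What remains is that the threshold applied to caregivers ignores that measure.

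*Attendance is a workable proxy.* The only scheduled events described for caregivers are the nurse consultations, and Table 2 gives the 6-month one a single aim, guidance on ending the role. Counting consultations is a reasonable measure of counseling received. It is not completion of a 6-month role, and the Adherence row already measures it.

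*A looser limit under a stricter one is not an error in itself.* When adherence fails, the limit still separates caregivers who missed a little from those who missed a lot. That stands. But once adherence passes it adds nothing, and a reader might go further and say it can never fail. That needs the same denominator for both criteria, which is the natural reading because both refer simply to informal caregivers, but is not stated.

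*Any caregiver who quits halfway is retained.* This reading is too strong. It holds under every set of visits only after the 3-month consultation. If the three visits are 1, 3 and 6 months, leaving between months 1 and 3 is scored as lost.

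*Weight in the overall decision.* A reader might infer that feasibility would be declared with most pairs dissolved. The Feasibility text names acceptability and adherence as the domains evaluated, and the loss limit appears only in Table 3. It does stand there as a feasibility criterion, however, whereas resource consumption is marked as not applicable. Patient adherence is a separate check, but it asks for weekly contact in 8 of 12 weeks and so does not cover late withdrawal.

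*The probabilities rest on assumptions.* They do. Visits missed by caregivers still in the role would raise the number scored as lost and lower the written rule's pass probability.

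**Conclusion.** The caregiver pass mark departs from the measure defined in its own row. Two consequences follow from the text without modelling: a caregiver who leaves after the 3-month visit is scored both adherent and not lost, and, given a common denominator, the limit is met whenever caregiver adherence is met. It therefore gives no independent verdict on caregiver retention, although the non-completion percentage remains a listed measure.

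The practical size depends on when caregivers leave and which three visits are meant. Under the illustrative model, 40% non-completion would usually pass the written limit and usually fail one set on completion. At 50% the written rule's result turns mainly on the unstated choice of visits. This is a correctable fault in one prespecified threshold and is worth correcting before the criteria are applied. It does not invalidate the feasibility assessment as a whole.

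**What to change.** Replace the caregiver limit in the loss-to-follow-up row of Table 3 with: *A maximum of 25% of informal caregivers who entered do not complete the 6-month program.* This fixes the denominator and uses the row's own measure. Record withdrawal status at the existing nurse contacts, and say in advance how a caregiver whose status is unknown because of a missed contact is counted.

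Keep consultation attendance under Adherence only. In the same edit, reconcile the three-versus-four consultation counts across Table 3 and the text. Reconciling the counts alone would not be enough, because loss would still be scored by attendance.

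The cost is one line of the table and one status item at contacts already planned. The downside is that reported caregiver loss may look less favourable.
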